### 3. STUDY DESIGN

The study is designed as a cluster-randomized controlled trial (RCT), which will compare patients who receive CAHE and with those who only receive usual care. We will collect data on the level of the patient, but randomize at the level of health care centres. The main reason for choosing a RCT with cluster randomization instead of a RCT with randomisation at patient level is that with the latter study design contamination can easily occur between the intervention and control groups.

On the basis of an analysis of numbers of patients, four health care centers (clusters) are required for this study, two for the intervention arm and two for the control arm. Important selection criteria for health care centers are that they should treat a sufficient number of patients from the target groups and that the hypertension care takes place according to the NHG standard CVRM.

The four health centers participating in the study will be randomly assigned to the intervention arm or the control arm (1 to 1 ratio).

The randomization will be performed by an employee of the Data Management Services team of the KEBB department of the AMC who is not involved in the study and blinded to the identity of the practices. In the health centers that are assigned to the intervention arm enrolled patients will get the CAHE. In the health centers that are assigned to the control arm enrolled patients will get the usual care which is provided in the health care centers. It is assumed that intercluster variance will be low. Based on the inclusion criteria and the fact that patients are treated with the same standard NHG in all four centers, we assume that differences in the mean blood pressure of hypertensive patients from the four centers will be low. Because the intra-cluster correlation coefficient is a ratio of the low between cluster variation and the within cluster variation, the intra-cluster correlation (ICC) is estimated to be <3%.

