### **4.4 Sample size calculation**

Four health care centers will be needed for the study and cluster-randomization. We assume a low between-cluster variance because of the homogeneity of demographic characteristics of the patient populations and treatment approaches of the participating health care centers. Based on the inclusion criteria and the fact that patients are treated according to the same clinical guideline (NHG), we assume little variation between the average blood pressures of hypertensive patients with an inadequately controlled BP. Because the intra-cluster correlation coefficient (ICC) is a ratio of the low between-cluster variation and within-cluster variation, we assume an ICC of  $< 3\%$ . The primary outcome measure will be a decrease in SBP at 8 months. A decrease of 10 mmHg (standard deviation = 15) in the intervention group compared to the control group will be considered as clinically relevant. To demonstrate this difference statistically with a reliability of the 5% chance of Type 1 error and a power of 80%, an average cluster size of 30 patients per cluster (health care centre) is needed. We strive to recruit a total 120 patients: 60 patients per treatment arm. Assuming an average dropout rate of 50%, 240 participants will have to be recruited.

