### **8.2 Univariate analysis**

Analysis of the primary outcome data: the systolic blood pressure measured at baseline minus the systolic blood pressure measured at 8 months past baseline.

All data entries will be controlled at random to avoid potentially incorrect codings. Univariate analyses will be conducted on the corrected database to compare variable distributions and identify positive or negative outliers. The analysis of the primary outcome measures will be carried out according to the 'intention to treat' principle. The primary outcome measure is calculated for each patient. Then the average within-group difference will be calculated for patients in the intervention group and the control group. Subsequently, the between-group difference between the calculated within-group differences will be calculated with a corresponding confidence interval. A decrease in systolic blood pressure by 10 mmHg (standard deviation = 15) in the intervention group as compared to the control group, with a confidence level of 5% probability of a Type 1 error, is considered to be clinically relevant. The analysis will use univariate and adjusted multilevel analysis.

The secondary data are analyzed in the same way.

If possible, separate subgroup analyses will be carried out by ethnic group and gender. For all analyses, a p value of 0.05 is used as the critical value. In subgroup analyses will be an adjustment to the p value for the number of analyses performed.

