### **8.3 Multivariate analysis**

Differences in the blood pressure values between treatment arms will be analyzed using a mixed model regression analysis that will take the dependence of the data and the intraclass correlation between centers into account. Corrections will also be performed for any differences in baseline characteristics of patients between the treatment arms.

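### Sections 8.2 and 8.3 give two analyses of the primary outcome without saying which decides; read literally, the 8.2 interval ignores centre, and its type I error can reach about 15% within the protocol's ICC range

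*Protocol*

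**What the plan says.** Section 3 states that "four health care centers (clusters) are required for this study, two for the intervention arm and two for the control arm", and that "the intra-cluster correlation (ICC) is estimated to be <3" per cent. Section 4.4 repeats that ICC bound. It takes as clinically relevant "A decrease of 10 mmHg (standard deviation = 15) in the intervention group compared to the control group", and plans for 5% type I error and 80% power with an average of 30 patients per centre. That makes 60 per arm and 120 in all, doubled to 240 recruits for 50% dropout.

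Section 8.2 sets out the primary comparison in steps: a change for each patient, an average of those changes in each arm, and then "the between-group difference between the calculated within-group differences will be calculated with a corresponding confidence interval". None of these steps mentions centre. Later in the same paragraph it adds: "The analysis will use univariate and adjusted multilevel analysis". Secondary outcomes are to be handled likewise, and "For all analyses, a p value of 0.05 is used as the critical value".

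Section 8.3 says that blood pressure differences between arms will be analysed by a "mixed model regression analysis that will take the dependence of the data and the intraclass correlation between centers into account", with correction for baseline differences. It names no estimation method, reference distribution or degrees of freedom.

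**The concern.** The unit of randomisation is the centre. An interval on the difference of two patient-averaged changes, with a standard error based on patients, treats 120 people as independent when the comparison rests on two centres against two. If outcomes within a centre are correlated at all, that interval is too narrow.

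The protocol also offers a centre-aware model for the same outcome and does not rank the two. With 5% as the threshold for every analysis, two analyses with different error rates both stand, and the more favourable one could be quoted as the main result. The sample size section plans for clustering, so the literal 8.2 interval is also at odds with the protocol's own reasoning.

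A mixed model does not settle the matter by itself. Four centres less two arm means leave 2 degrees of freedom for the between-centre variance, and large-sample tests perform poorly there.

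**Working it through.** **Inputs.** Difference 10 mmHg, SD 15, 5% type I error, 80% power, 30 per centre and ICC below 3% (sections 3 and 4.4); two centres per arm (section 3). Assumptions: two-sided test, equal centre sizes, normal data, SD 15 as the SD of the analysed change, and the ICC applying to that change. The error rates do not depend on the SD; power and interval width do.

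**1. Reproduce the planned size.** Without clustering, n per arm = 2 × (1.96 + 0.842)² × 15² / 10² = 35.3. With design effect DEFF = 1 + (30 − 1) × ICC, 60 per arm needs DEFF = 60/35.3 = 1.70, so ICC = 0.70/29 ≈ 0.024. The bound of 3% allows that value. At ICC 0.03, DEFF = 1.87 and 35.3 × 1.87 = 66 per arm would be needed; 60 per arm gives 76% power by the same normal formula. Dropout: 120/(1 − 0.5) = 240, as stated.

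**2. Pooled patient-level interval.** Its standard error is too small by √DEFF, so its type I error is about 2 × [1 − Φ(1.96/√DEFF)]. At ICC 0.03, √1.87 = 1.37, 1.96/1.37 = 1.43, and the error is 15.2%.

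**3. Simulation.** 2,000,000 null trials per setting, four centres of 30. The mixed-model column assumes REML, a Wald z and a centre variance that cannot go below zero.

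| ICC | Pooled patient-level | REML, Wald z | t test on four centre means, 2 df |
|---|---|---|---|
| 0 | 5.0% | 3.9% | 5.0% |
| 0.01 | 8.5% | 6.0% | 5.0% |
| 0.02 | 12.0% | 7.8% | 5.0% |
| 0.024 | 13.3% | 8.4% | 5.0% |
| 0.03 | 15.3% | 9.3% | 5.0% |

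At ICC 0.03 the centre variance is estimated as zero in 40% of trials, and the model then falls back on the patient-level analysis. Maximum likelihood in place of REML would give about 13%. If nobody dropped out (60 per centre), the pooled and REML rates at ICC 0.03 would be 24% and 12%.

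**4. Cost of a valid test.** With two centres per arm, the standard error of the difference is 15 × √(DEFF/30).
- ICC 0.03: SE = 15 × √(1.87/30) = 3.75. The noncentrality is 10/3.75 = 2.67; with t on 2 df (critical value 4.303), power is about 33%.
- ICC 0: SE = 15 × √(1/30) = 2.74. The noncentrality is 3.65 and power is about 50%.
- Between these, power is about 43% at ICC 0.01 and 37% at ICC 0.02.
- The 95% half-width at ICC 0.03 is 4.303 × 3.75 = 16.1 mmHg at the true standard error. The estimated standard error on 2 df averages 0.886 of the true one, so the average half-width is about 14 mmHg.

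**The case against.** The strongest reply is that the protocol does handle clustering. The sentence on the interval defines a contrast and gives no variance formula. The same paragraph brings in multilevel analysis, perhaps meaning that both the unadjusted and the adjusted analyses are multilevel, and section 8.3 says outright that centre correlation is taken into account. The test and its degrees of freedom are details commonly left to a statistical analysis plan, which is not shown here.

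Much of this stands. A reader might infer that the protocol fixes a pooled interval as its primary result, with a 15% false-positive rate, and a mixed-model test with 9%. The documents do not support that. The pooled interval is the literal reading of section 8.2 but not the only one. The ICC is an upper bound, so 15% and 9% are ceilings over the stated range at 30 per centre. The 9% also depends on a test the protocol never names, and the absence of a degrees-of-freedom method is not in itself a fault.

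What the reply does not remove is that the protocol writes out a procedure with no place for centre, sets a centre-aware model beside it for the same outcome, and leaves open which one decides. An analysis plan that followed section 8.2 to the letter would carry that interval forward.

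**Conclusion.** The point holds in a limited form. Sections 8.2 and 8.3 leave the deciding primary analysis unnamed, and the interval in section 8.2, read literally, cannot keep the 5% error rate in a trial of four randomised centres unless the ICC is zero.

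Its type I error runs from 5% at ICC 0 to about 15% at ICC 0.03, and is about 13% at the ICC that reproduces the protocol's own sample size. For the mixed model the corresponding range is about 4% to 9%, conditional on REML with a Wald z. These figures assume 30 patients in every centre; unequal centres, likely with 50% dropout, would shift them somewhat.

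It would be wrong to conclude that a better test alone repairs the trial. A test that respects four centres restores the 5% error rate but not the 80% power.

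**What to change.** - In sections 8.2 and 8.3, name a single primary analysis: the baseline-adjusted comparison that accounts for centre, with inference valid for four clusters. One example is a t test on the four adjusted centre means with 2 degrees of freedom. A mixed model whose centre variance may go below zero is exactly equivalent only when centres are of equal size. Keeping the variance truncated at zero and using t on 2 df over-corrects, with a type I error of about 0.1% at ICC 0.03.
- Delete the patient-level interval of section 8.2, or label it descriptive.
- Apply the same rule to the secondary outcomes, which section 8.2 ties to the primary method.
- Restate the power in section 4.4 for the chosen analysis.

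The wording takes a few sentences, but the consequence is large. The 95% interval would average about 14 mmHg either side of the estimate at ICC 0.03, wider than the 10 mmHg target. Power would be about 33% at ICC 0.03 and 50% at ICC 0, against the 80% claimed. These figures give no credit for any SD reduction below 15 from baseline adjustment, which the protocol does not quantify.

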#### **6.1.2. Secondary study parameters / endpoints (if applicable)**

Difference between baseline and 8 months past baseline regarding the following measures:

- Adherence to medication
- Adherence to lifestyle advice
- Mediating factors that may affect the way in which patients manage hypertension:
  - o beliefs about hypertension and medication / lifestyle changes
  - o motivation to use / medication to carry out lifestyle changes
  - o self-efficacy to use / medication to implement lifestyle changes
- Satisfaction with care
- Baseline demographics of potential confounders, such as age, gender, ethnicity, environment and other socio-economic circumstances are included in the study.

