##### **Ad 3. Interview**

The research nurse or interviewer will collect questionnaire data, immediately following the physical examination. The interview will take place in the participant's preferred language (English or Dutch). The interview includes questions about:

1. Adherence to treatment with regard to medication
2. Adherence regarding lifestyle advice.
3. Health: patients ideas about their own health.
4. Hypertension: ideas about hypertension and the causes, the way one deals with hypertension, motivation to do something about hypertension, confidence (self-efficacy) in managing ;hypertension.
4. Medication; ideas about medication in general, ideas about antihypertensive medications, experiences in taking antihypertensive medications, intentions (motivation) for following medication advice.
5. Lifestyle advice: ideas about lifestyle changes, acquired experience in dealing with lifestyle advice, intentions (motivation) on the compliance of lifestyle advice: This involves exercise per week, diet, salt intake, smoking and alcohol consumption.
6. Treatment: Satisfaction with treatment/care.

During the baseline assesment, the following demographics of the patient will be collected: age, gender, ethnicity (birth parents and grandparents; self-identification), education, occupation, income, marital status, duration of residence in the Netherlands, hypertension duration, health insurance. This part of the questionnaire will not be included in the post-test. During the post-test it will be assessed if stressful events have happened between account possible T0 and the final assessment. This information can be used in the final analysis of the data in order to assess potential confounders or effect modification (eg change in income, marital status).

Underneath we will provide more detailed information on the questionnaires that will be used in the interview. Where possible standardized validated questionnaires will be used:

1. To measure self-reported measure medication compliance, we will use the four-item scale Morisky. (30) To measure social support for adherence to treatment we will use the validated social support scale, from the MOS (Medical Outcome Survey) which had been used by Ogedebge (31) in a similar study.
2. To measure compliance with regard to lifestyle advice, we use a modified Morisky scale per lifestyle advice. (30)

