#### *Medication Use*

Besides self-reported medication adherence, medication adherence will also be evaluated using pharmacy data. Thereby the number of times in which a prescribed recipe for anti-hypertensives is picked up in time will be used as a measure. Thi9s indicates 'refill adherence ". Refill adherence is defined as the number of days for which antihypertensives are supplied divided by the total number of days after which the patient collects his/her repeat prescription). (39) A patient is defined as dherent if t he repeat prescription is filled within 7 days of the designated date. This method is also used in other research. (40)

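### Section 8.2 analyses all secondary outcomes as raw change from baseline; baseline-adjusted 8-month values would be better, and refill adherence has no defined baseline

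*Protocol*

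**What the plan says.** Section 8.2 describes the primary analysis in steps. A baseline-minus-8-months difference is formed for each patient and averaged in each arm. The two averages are then set against each other: "Subsequently, the between-group difference between the calculated within-group differences will be calculated with a corresponding confidence interval". On the model, the section adds only this: "The analysis will use univariate and adjusted multilevel analysis". The rule for all other outcomes is one sentence: "The secondary data are analyzed in the same way".

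Section 6.1.2 introduces the secondary endpoints, including adherence to medication and to lifestyle advice, as "Difference between baseline and 8 months past baseline regarding the following measures".

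Section 8.3 gives the model: "Differences in the blood pressure values between treatment arms will be analyzed using a mixed model regression analysis". It accounts for correlation within centres and corrects for differences in baseline characteristics between the arms. It is written for blood pressure and lists no covariates.

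The adherence measures are described in section 6.3:
- Medication adherence by self-report uses a four-item scale in the interview, which is held both before and after the intervention.
- For lifestyle, "To measure compliance with regard to lifestyle advice, we use a modified" form of that scale, one for each advice, in the same interview.
- Pharmacy data supply a further measure of medication adherence. Under Medication Use it is defined as days supplied divided by days elapsed until collection. A patient is also classed as adherent if the "repeat prescription is filled within 7 days of the designated date".

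**The concern.** The sentence in section 8.2 is a stated rule and not a gap left for a statistical analysis plan, so it can be judged as it stands. It raises two issues.

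**Self-report scores.** A raw change score subtracts the whole baseline value. When baseline and follow-up are only moderately correlated, this over-corrects. It adds noise, and it credits an arm that happened to start worse with improvement that is regression to the mean. With four centres, two per arm, a chance difference between the arms at baseline is a practical possibility. The adjustment that the protocol mentions does not name the baseline adherence score.

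**Refill adherence.** Sections 6.1.2 and 8.2 together require a change from baseline. Medication Use gives two forms of the measure, does not say which is analysed, and sets no period before T0 over which a baseline would be obtained.

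At stake are the precision and interpretation of the results for the two secondary effectiveness objectives, and whether the pharmacy measure can be analysed by the stated rule at all.

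**Working it through.** **1. The plan's own figure.** The only sample size is for systolic blood pressure (section 4.4: difference 10 mmHg, SD 15, 5% type 1 error, taken here as two-sided, 80% power, 30 patients per centre, ICC below 3%).
- Individually randomised: n = 2 × (15 × (1.960 + 0.842) / 10)² = 35.3 per arm.
- Design effect 1 + 29 × ICC. Sixty per arm is reached at ICC = (60/35.32 − 1)/29 = 0.024, inside the stated bound.
- Dropout: 120/(1 − 0.5) = 240.

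The figures are reproduced, and nothing below changes them. No power is stated for any secondary outcome.

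**2. Is raw change valid for the self-report scores?** Section 6.3 gives these scores a baseline, so the change exists. Coverage of the 95% interval for a difference in mean change was simulated with 60 per arm, 4,000 replicates per setting and no clustering. Item probabilities (0.60 to 0.97) and yes/no item scoring are assumptions.

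| Outcome | Coverage |
|---|---|
| Four-item score, range 0–4 | 94.3% to 95.2% |
| Yes/no outcome that has a baseline | 94.7% to 95.4% |

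The contrast is valid on average, for bounded and for yes/no outcomes alike.

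**3. What raw change costs in precision.** Let b be the slope of follow-up on baseline. With equal variances at the two times, b equals the correlation, and the ratio of residual variances (raw change to baseline-adjusted) is 2(1 − b)/(1 − b²) = 2/(1 + b).

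For an assumed 0–4 score made of four yes/no items (latent correlation over time 0.6 or 0.8, no treatment effect, 33% to 59% of patients at the best score at baseline), simulation gave b = 0.38 to 0.57.
- b = 0.38: 2/1.38 = 1.45.
- b = 0.57: 2/1.57 = 1.27.

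The simulated ratios were 1.28 to 1.45, in agreement. On the standard-error scale this is √1.28 = 1.13 to √1.45 = 1.20, for the within-centre part of the variance only.

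**4. What raw change does with a chance imbalance.** If the arms differ at baseline by d and there is no treatment effect, the expected difference in change is d × (1 − b), in favour of the arm with the worse baseline. For an assumed d of 0.3 points:
- b = 0.57: 0.3 × 0.43 = 0.13 points.
- b = 0.38: 0.3 × 0.62 = 0.19 points.

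**5. Refill adherence, provisions side by side.**
- Sections 6.1.2 and 8.2 need a baseline value and an 8-month value.
- Medication Use offers a ratio and a yes/no class, with no choice between them and no baseline period.
- The retrospective items under Medical records include prescribed medication but no refill history.
- Baseline adherence is otherwise obtained only by interview.

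The required change therefore cannot be computed from the protocol as written.

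**The case against.** The strongest reply is that the same-way rule includes more than subtraction. Section 8.2 also promises adjusted multilevel analysis, and section 8.3 promises correction for baseline differences. That is fair, and the plan should not be read as wholly unadjusted. But section 8.3 is confined to blood pressure and depends on differences that are observed, and neither section names the baseline adherence score as a covariate. The reply narrows the point without removing it.

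Second, preferring baseline adjustment to change is a matter of efficiency, and the same argument could be made for blood pressure. This stands as a limit on severity: coverage is close to nominal.

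Third, some stronger readings are tempting, and the document does not support them.
- A reader might infer that refill adherence is simply yes/no and that the rule cannot work for it. Medication Use also defines a continuous ratio, for which a mean change is an ordinary analysis, and even a yes/no outcome can be differenced once it has a baseline. The missing period before T0 is silence. Nothing rules out retrospective pharmacy data.
- A reader might blame the change score for a ceiling effect. Patients at the best score cannot improve under any model; that belongs to the instrument.
- A reader might object that non-smokers have no smoking-adherence score. They would have none under any model. Who enters each lifestyle analysis is detail that a statistical analysis plan may supply.

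**Conclusion.** The point holds in a limited form and is minor. Section 8.2 fixes raw change for every secondary outcome where a better analysis of the same data is available at almost no cost.

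For the self-report scores the loss is a residual variance about 1.3 to 1.45 times larger, plus a carry-over of 0.13 to 0.19 points for each 0.3 points of chance baseline imbalance. These sizes rest on assumptions that the protocol does not supply: the 0–4 range, the correlation over time, the share of patients at the best score, and the 0.3-point imbalance. The carry-over also assumes that a difference between centres regresses at the same rate as differences between patients. The direction of both effects needs only a slope below 1.

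For refill adherence the defect is an unresolved choice of form and an undefined baseline, not an analysis that is impossible. It touches one supplementary measure under the medication objective and does not reach the lifestyle objective. It would be wrong to infer that the secondary results would be invalid.

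**What to change.** Replace the one-sentence rule in section 8.2 with the following.
- **Self-report and other secondary scores:** the 8-month value is the outcome and the same score at baseline is a named covariate, with centre handled as for the primary outcome. This also fits the wording of secondary objectives 2 and 3 in section 2, which speak of differences between the arms at 8 months.
- **Refill adherence:** state in advance whether the ratio or the yes/no form is the endpoint, and compute it over the follow-up period. Compare the arms with a model suited to the form chosen (linear mixed for the ratio, logistic mixed for yes/no), adjusted for refill before T0 where pharmacy records allow.
- **Section 6.1.2:** align the introductory line so that it no longer requires a difference from baseline for every measure.

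The cost is a few lines of text and slightly more analysis work. No further contact with patients is needed; the pre-T0 refill adjustment depends on what the pharmacy records hold. The primary analysis and the sample size do not change.

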## **4. STUDY POPULATION**

### **4.1 Population (base)**

#### **Practices**

A total of 240 patients who are diagnosed with hypertension and meet the inclusion criteria will be recruited from the participating general practices (health care centers). It is expected that the following practices will participate in the study: two GAZO-centers: "Reigersbos" and "Klein Gooioord" and two other centers in the 'high Bijlmer' neighborhood. We choose these practices because they are located in a region where relatively many Afro-Surinamese and Ghanaians are living. The first two centers that are part of the GAZO foundation (Healthcare centres Amsterdam South East), have an estimated number of 401 Afro-Surinamese and 75 Ghanaian patients with hypertension (K86 + K87). As other health care centers, 75 in Amsterdam South East we are considering Kraaiennest and a center to be determined). The latter two centers are located in the "high Bijlmer", the neighbourhood where the with the highest number of Ghanaian and Surinamese population in Amsterdam South East. Based on data from the SUNSET study, (6) we assume that about 63% of the patients who are treated for HTN will have a BP above the target values ( $\geq 140/90$  mm Hg at two measurements)

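### Section 8.2 plans separate subgroup analyses by ethnic group and gender, but names no test of whether the effect differs between the subgroups

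*Protocol*

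**What the plan says.** Section 8.2 states: "If possible, separate subgroup analyses will be carried out by ethnic group and gender". The decision rule follows directly: "For all analyses, a p value of 0.05 is used as the critical value", and then "In subgroup analyses will be an adjustment to the p value for the number of analyses performed". The adjustment method is not named.

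Section 8.3 analyses blood pressure with a "mixed model regression analysis that will take the dependence of the data and the intraclass correlation between centers into account", corrected for baseline differences. It mentions no treatment-by-ethnicity or treatment-by-gender term. Effect modification appears once, in section 6.3 under the interview. There it concerns stressful events between baseline and the final assessment, and no method is given.

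On subgroup size, section 4.1 says that the first two centres "have an estimated number of 401 Afro-Surinamese and 75 Ghanaian patients with hypertension". It gives no split for the other two centres, and no gender split is given anywhere.

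**The concern.** Separate analyses judged by p value invite the reading that the education works in the group with a significant result and not in the other. That comparison is not a test. Two subgroups with the same true effect can fall on opposite sides of the threshold because of size or chance alone.

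The trial enrols two ethnic groups and evaluates education tailored to both. Readers will therefore look for whom it works. A result in one group only, produced by the sample split, could be taken as evidence that the education fails in the other group.

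**Working it through.** **Inputs.** Section 4.4 gives the effect and SD ("A decrease of 10 mmHg (standard deviation = 15) in the intervention group compared to the control group will be considered as clinically relevant"), the error rates ("with a reliability of the 5% chance of Type 1 error and a power of 80" per cent), 30 patients per centre and 60 completers per arm. Section 3 has four centres, two per arm, and says "the intra-cluster correlation (ICC) is estimated to be <3" per cent. Section 4.1 gives 401 and 75 patients. Assumed: two-sided tests, normal approximation, the same subgroup mix in every centre, and Bonferroni over four tests (0.05/4 = 0.0125) as the strictest form of the adjustment.

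**The plan's own figure.** n per arm = 2 × 15² × (1.960 + 0.842)² / 10² = 35.3. The design effect is 1 + 29 × ICC. At ICC 0.024, 35.3 × 1.696 = 59.9, so 60 per arm, 120 in total, and 120/0.5 = 240 recruited. The stated figures reproduce for an ICC inside the stated limit. They size the overall comparison only.

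**Ethnic subgroups at 401:75.** Ghanaian share = 75/476 = 15.8%. Per arm, 60 × 0.158 = 9.45 Ghanaian and 50.55 Afro-Surinamese completers.

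- SE of the treatment difference = √[225 × ICC + 2 × 225 × (1 − ICC)/n].
- ICC 0: Ghanaian SE 6.90 (95% CI about ±13.5 mmHg), Afro-Surinamese SE 2.98.
- ICC 0.03: Ghanaian √(6.75 + 436.5/9.45) = 7.27; Afro-Surinamese √(6.75 + 436.5/50.55) = 3.92.
- Power = Φ(10/SE − 1.96), the other tail being negligible. ICC 0: 0.305 and 0.918. ICC 0.03: 0.280 and 0.722.
- Chance that exactly one is significant, ICC 0: 0.918 × 0.695 + 0.305 × 0.082 = 0.66.
- ICC 0.03, treating the two results as independent: 0.722 × 0.720 + 0.280 × 0.278 = 0.60. The two groups share their centres' effects, and allowing for this by simulation gives 54 to 55%.

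**Other splits**, with a 10 mmHg effect in both subgroups and alpha 0.05:

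| Share of smaller subgroup | ICC 0 | ICC 0.03, independent | ICC 0.03, shared centre effects |
|---|---|---|---|
| 15.8% | 66% | 60% | 54–55% |
| 25% | 54% | 54% | 47% |
| 40% | 42% | 50% | 40% |
| 50% (also gender, if equal) | 39% | 49% | 39% |

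**Smaller common effects** (ICC 0, alpha 0.05). At the 401:75 split the chance is 66% at 10 mmHg, 63% at 7.5, 41% at 5 and about 10% at 0. At an equal split it is 39%, 50%, 38% and about 10%. It peaks there near 7.5 mmHg, because each subgroup then has about 50% power.

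**What the adjustment does** (alpha 0.05 to 0.0125):

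- Ethnicity at 401:75, 10 mmHg, ICC 0: 66% rises to 71%.
- The same at ICC 0.03: 60% falls to 52% (independent), or about 54% to 47% (shared centre effects).
- The same split at ICC 0 with 5 mmHg: 41% falls to 23%.
- Gender, equal split, 10 mmHg: 39% rises to 50% at ICC 0. At ICC 0.03 with shared centre effects it falls from 39% to 37%.
- No effect: about 10% falls to 2.5% per factor.

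**Interaction test instead.** With identical effects, a false declaration of a difference occurs in 5% per factor (simulated 4.8 to 5.3%). Power for a true 10 mmHg difference between subgroups at ICC 0:

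- 401:75: SE = 15 × √(2/9.45 + 2/50.55) = 7.52, power 26%.
- Equal split: SE = 15 × √(4/30) = 5.48, power 45%.

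**The case against.** The protocol does not say that significance in one subgroup will be compared with significance in the other, or that a differential effect will be claimed from it. The analysis is conditional on being possible, and about nine Ghanaian completers per arm might itself rule it out. Section 2 asks about subpopulations only for participation and feasibility, not for effect. An analysis plan that is not shown could add interaction terms. All of this limits the consequence. It does not remove the point, because section 8.2 states a method and a p-value rule, and that method cannot answer the question that subgroups by ethnicity and gender raise.

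Four stronger readings are tempting, and the documents do not support them:

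- A reader might infer that the p-value adjustment makes matters worse. It does so at ICC 0 with a 10 mmHg effect, but at 0.0125 it lowers the one-group-only risk at ICC 0.03 and for clearly smaller effects.
- A reader might infer that all the subgroups are very unequal. Only ethnicity has a documented split, at two of four centres, and it counts patients before the blood-pressure and diabetes criteria.
- A reader might infer that a one-group-only result is likely whenever effects are identical. That needs a common effect of some size. With none, the chance is about 10% per factor at 0.05.
- A reader might take the ICC 0 figures as cautious. At the 401:75 split, ignoring clustering gives the top of the range.

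The figures also depend on the test used. If each subgroup were tested on centre means with 2 degrees of freedom, the chance would be 34 to 46% per factor at 0.05 and 12 to 17% at 0.0125, because both subgroups would then usually fail.

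**Conclusion.** The point holds as one about interpreting exploratory subgroup results. If the design effect is real and equal in every subgroup, roughly four to six and a half trials in ten would show significance in exactly one of the two ethnic groups at 0.05, with no true difference. The upper part of that range rests on the 401:75 split applying to the whole trial. For gender the chance is about four to five in ten, on an assumed equal split. The 49% end treats the sexes as independent at ICC 0.03, and allowing for shared centres brings it back to about 39%.

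These figures assume two-sided normal-theory tests, SD 15, 60 completers per arm and an ICC of at most 0.03. Nothing here touches the primary comparison or the sample size. It should be corrected, but the trial does not depend on it.

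**What to change.** In section 8.2, replace the separate subgroup tests with a treatment-by-ethnicity term and a treatment-by-gender term in the mixed model of section 8.3. Report each interaction estimate, and the subgroup effects from the same model, with confidence intervals. Label them exploratory, and state that no claim of a differential effect will rest on within-subgroup p values.

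The cost is a sentence or two of text and two model terms, with no new data. The downside is low power, about 26 to 45% for a true 10 mmHg difference between subgroups. Most results will be inconclusive, and the text should say so in advance: a non-significant interaction is not evidence that the effects are equal.
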